**University of Liverpool**

**Executive Summary:**

Premature delivery makes a large contribution to perinatal and infant mortality and disability. Recurrent pregnancy loss through prematurity may also produce significant risk to the mother in resource-poor areas where the risks of maternal mortality and morbidity are high. We have previously found a very high risk of premature labour and delivery (20-25%) in a rural area of Malawi, Namitambo. Uniquely this was a rural community based study in which all women had gestational age established with precision by ultrasound examination in early to mid pregnancy. It is well established that infection may cause premature labour, and we found a high prevalence of vaginal infection in this community as well as biochemical evidence of chronic infection. Previous work in Kenya (in urban populations that did not have gestational age confirmed by ultrasound) has suggested that antibiotic prophylaxis could improve outcome of pregnancy in populations with high burdens of infective disease. We propose therefore to perform a randomised, placebo-controlled trial of an antibiotic intervention at 16-20 and 28-32 weeks of pregnancy. The primary outcome measures in the trial will be the incidence of preterm birth and the mean gestational age at delivery. We will at the same time study the possible impact of antibiotic prophylaxis on maternal anaemia – as previous studies have suggested that chronic infection may be important in the aetiology of anaemia in pregnancy. We will also explore views among women (and men) on premature labour and fetal and neonatal loss.

# Introduction and Rationale:

In developing countries perinatal mortality continues to be unacceptably high with estimates for sub-Saharan Africa ranging between 45 and 75 per 1000 1, compared to 8 per 1000 for the UK. The major cause of perinatal death world-wide is pre-mature (pre-term) delivery (i.e. at < 37 weeks gestation). The incidence of premature delivery in most industrialised countries is reported to be around 7%, but there are few reliable data from sub-Saharan Africa. We have recently completed a Wellcome Trust supported randomised trial of Vitamin A supplementation in pregnant, anaemic women in a rural community in Malawi (Namitambo) and, unexpectedly found a very high incidence of premature labour among participants. Gestational age was determined by ultrasonography before 24 weeks gestation. Mean gestational age at booking (= first antenatal clinic visit) was 20.6 weeks (s.d 3.5). Information about delivery was available for 589 women. For women who were non-anaemic at booking premature delivery was recorded in 20.7% of cases, for anaemic women ([Hb] < 11.0 g/dl) premature delivery was recorded in 24.7% of cases and for women with sever anaemia ( [Hb] < 8.0 g/dl) prematurity was recorded in 29.7% of cases. 2, 2b All of these women had, by virtue of entry criteria to the study, singleton pregnancies (multiple pregnancy carries a particularly high risk of preterm delivery). They also received oral iron and folic acid supplementation, and two routine doses of anti-malarial prophylaxis (SP) in the antenatal clinic. Importantly this was a population which had undergone mid-pregnancy ultrasound dating as part of the research protocol, so the gestational age at delivery was not in doubt. Many studies have used low birth weight (i.e. <2.5 kg) as a surrogate measure of prematurity but this index cannot distinguish between preterm birth and fetal growth restriction. We are aware of only one other such study in Africa with ultrasound dating; this was done in an urban centre (Maputo, Mozambique) and reported a 15% incidence of preterm delivery with low maternal weight gain and malaria as major risk factors 3. Another study in rural Malawi (Mangochi) 4 described a 22% incidence of premature delivery in an unselected population, but gestational age assessment was based on tape measure of symphysis-fundal height (uterine size) - a method recognised as inaccurate in determining the duration of pregnancies.

The consequences of a high incidence of preterm delivery are considerable because of the contribution to neonatal mortality – 30% in one rural area of the Gambia 5 and 65% in the Mangochi study in Malawi4. In a series from Tanzania, 52% of all babies with respiratorydistress syndrome (closely associated with prematurity) died6. Prematurity also makes an important contribution to later, infant mortality, at least as significant a contribution as maternal HIV infection in one recent report from Malawi7. Where the facilities exist in hospitals for neonatal care, prematurity represents the major indication for special care, with significant health cost consequences. 8,9

Prematurity is also well recognised as conferring long-term neuro- developmental disadvantages that include, at one end of the spectrum, cerebral palsy, and at the other more subtle educational and social difficulties. It is clearly undesirable for populations already disadvantaged by poverty and high burdens of disease, to also cope with the short and long term consequences of preterm birth.

There may be an additional dimension to the problem that has not, to our knowledge been highlighted before. Women who have had one premature delivery are at increased risk of this complication recurring in future pregnancies. It is now well recognised from epidemiological work that the dangers associated with high parity are in part explained by the efforts of women at reproductive disadvantage to achieve their desired family size. It is important to investigate this possibility in Namitambo because of the much higher risk of maternal death and morbidity per pregnancy in rural Malawi – we would like to explore this further and will obtain both women’s and men’s views on these issues.

Since our population in Namitambo were all anaemic for entry into the Vitamin A trial, the possibility has to be considered that the anaemia per se was responsible for the high rates of premature delivery (we have found 72% of this population to be anaemic during pregnancy as defined by a haemoglobin < 11 g/dl)10. In fact the link between anaemia itself and preterm delivery is, at best, weak. A large UK study found that the incidence of preterm delivery was 9.7% in women with haemoglobin levels < 8.5 g/dl compared with the national average of 7% and incidences at high haemoglobin levels of 13.5-14.5 g/dl and >14.5 g/dl were respectively, 12% and 22.5% 11. We hypothesise that any association between anaemia and premature delivery in the Namitambo population is indirect and explained by a common link of chronic infection. We have also found, in Namitambo, that 20% of anaemic women had no demonstrable deficiencies of iron, Vitamin A, folate or Vitamin B12, but more than half of these women had high C reactive protein (CRP) levels, a marker of infection 12. Similarly in 73% of iron-replete but anaemic women, there were high levels of CRP, suggesting that chronic infection might be responsible for physiological failure to mobilise iron stores. In the Vitamin A trial, we found 74% of women to have CRP levels > 5mg/dl and 23% to have levels > 20 mg/dl. In HIV +ve women in Namitambo we found anaemia to be more common than in HIV –ve women, but could find no nutritional basis for the differences. 13

There are compelling data to link infection, and especially, lower genital tract infection with preterm labour and delivery.14-16. We have recently completed a survey of genital tract infection in the pregnant population of Namitambo and this is currently being analysed. 1000 women were screened by venepuncture and vaginal speculum examination for high vaginal and endocervical swabs for microbiological studies. Currently available results have been obtained from the first 565 and showed 10% to be VDRL (+ve) (syphilis), 21% to be HIV positive, 3% to have asymptomatic urinary tract infection, 78% to have abnormal vaginal microbiology, including candidiasis 40%, trichomonas 25% and clue cells (bacterial vaginosis) in 17%. We were unable to test for gonorrhoea but found pus cells in 15% of women screened. Chlamydial testing will be completed in the laboratory shortly. This is thus a population with a high prevalence of abnormal vaginal flora. (unpublished information). Importantly there was no relationship between reported symptoms and/or findings on speculum examination and type or severity of infection. It has been known for some time now that the ‘syndromic approach’ to treatment of sexually transmitted infections in women is poor in accuracy. This may be particularly so in pregnancy when vaginal discharge is also noted to be different as a result of hormonal changes.

The biochemical and cellular events that occur at the time of labour resemble an inflammatory response with, in particular, cytokine release (notably IL-6 and TNF) 17. Women in labour have raised serum IL-6 concentrations; in women whose labour is premature labour and is associated with intrauterine infection, IL-6 is extremely elevated. 18 IL-6 stimulates the production of Prostaglandin E2 that in turn stimulates uterine contractions and cervical ripening. Similarly TNFa is elevated in preterm labour, and very elevated if this is associated with microbial invasion of the amniotic cavity 19.

There are only two trials of untargeted antibiotic prophylaxis (i.e. not targeted at specific cultured micro-organisms) in African pregnant populations with high prevalence of lower genital tract infections including sexually transmitted infections. Both studies were performed in urban populations in Nairobi, Kenya, by the same research team. In the first study 20, 400 women were randomly allocated to receive a single dose intramuscular injection of a cephalosporin antibiotic at an estimated 28-32 weeks of pregnancy or placebo. Mean birth weight was greater in the antibiotic arm (3209 g vs 3056 g) and, though there were fewer low birth weight babies (4.0 % vs 9.3%) this difference did not reach conventional levels of statistical significance. The second trial 21 specifically addressed high risk pregnant women; 320 women with poor obstetric histories (including histories of previous preterm deliveries) were randomly allocated to receive the same antibiotic treatment as the first study, or placebo. There were statistically significant increases in mean birth weight (2927g vs 2772g) and decreases in the number of low birth weight babies (18.7% vs 32.8%) among women in the antibiotic treated arm. Mean gestational age at delivery was not statistically, significantly different but in both trials most women were offered treatment for the first time late in pregnancy (third trimester) and the authors acknowledge the uncertainties of gestational age estimation in their study populations.

These findings are sufficiently encouraging to support a further trial in a similar population with high levels of infection but with gestational age firmly established by mid-pregnancy ultrasound examination- the Namitambo-Chiradzulu field site would provide the ideal setting. If the Kenyan findings are confirmed, this would provide important information for health promotion in lager areas of Africa and elsewhere.

Antenatal coverage in the Namitambo-Chiradzulu area is excellent with 95% of women attending antenatal and postnatal clinics. An average of 5.2 (sd 2.6) clinic visits is made during pregnancy.22 Most women (63%) deliver at the health centre or district hospital. In 19% of cases assistance at delivery is by an untrained traditional birth attendant at home and in 16% of cases assistance at delivery is by a female relative. The rest of the deliveries are unattended.22 Women who deliver at home are usually seen at nearest health centre in the first week post delivery as part of postnatal care.

Perinatal mortality is estimated at 30 per 1000 births, and maternal mortality at 413 per 100,000 deliveries.22 Women between the ages of 15 and 45 were interviewed and asked about pregnancy outcome; 8.9% of women reported the loss of at least one pregnancy before 7 months, 8% had lost a pregnancy after 7 months and 4.3% of women reported the loss of a baby within the first 24 hours of birth. Gestational age is not defined in weeks in this population but culturally a distinction is made between loss before or after ‘7 months’ of pregnancy.

# Objectives of the study

- To confirm the high incidence of premature labour and delivery in an unselected, rural pregnant population in southern Malawi (Namitambo-Chiradzulu) in whom gestational ages had been determined by ultrasound.
- To determine the effects of prophylactic treatment with antibiotic given at 16-22 and 28-32 weeks of pregnancy on premature delivery, gestational age at delivery, perinatal mortality, maternal anaemia, and other pregnancy outcomes, by a randomised controlled trial.
- To explore knowledge of, and attitudes to, premature labour and fetal and neonatal loss among women and men in the Namitambo area.

# Methods

We propose a randomised placebo-controlled trial to assess the significance of infection as a cause of prematurity, and to test a possibly effective intervention strategy in this high-risk population. Women will be eligible for entry into the study if they have a single viable pregnancy with fetal measurement (biparietal diameter) < the mean for 24 weeks gestation - gestational age is accurate to within 10 days at this phase of pregnancy. Standard obstetric epidemiological data, including those denoting increased risk of premature delivery will be noted.

Women will be randomly allocated by opening a sealed, numbered pre-prepared envelope to one of the two interventions. In the experimental arm they will receive antibiotic treatment on a single occasion between 16-24 weeks (at the time of booking) and again as a second single dose between 28 and 32 weeks (the time of the intervention in the Kenyan studies). Women in the control group will receive oral placebo on both occasions.

For the antibiotic, we propose to use **Azithromycin** **1 gram** given as a single oral dose. Azithromycin is chosen because of its wide spectrum of activity against micro-organisms likely to be associated with preterm labour.23 It also has the advantage of single dose administration, and will likely become less expensive in the near future as the patent expires.

Azithromycin is safe in pregnancy. It is a macrolide antibiotic which is active against a wide range of organisms which are associated with premature labour including, *Neisseria gonorrhoeae*, *Escheridia coli,* *Salmonella* spp., *Chlamydia* and bacterial vaginosis. In addition it is active against gram-negative organisms that have been associated with adverse pregnancy outcome including B haemolytic- streptococci and *Bacteroides spp*.23 Azithromycin is similar to erythromycin but has greater activity than erythromycin against gram-negative bacteria and improved pharmacokinetics with the added advantage that it can be given as a single dose. Mild gastro-intestinal side effects have been noted but otherwise Azithromycin is very well tolerated.23 The gastro-intestinal side effects were noted in one study where 2g doses were given and vomiting was reported in up to 8% of patients. We will give a 1g dose under direct supervision and ask women to report any side effects noted.

There is some very recent evidence that azithromycin may also have a protective effect against malaria (personal communication, Pfizer April 2002). We will therefore also monitor malaria parasitaemia during pregnancy.

In addition to antibiotic treatment or placebo all women will receive daily supplements of iron (with folic acid) as well as the recommended two doses of SP as presumptive treatment for malaria. Antenatal and postnatal care will be provided in accordance with current Ministry of Health and Population (MOHP) guidelines. Vitamin A 200 000 IU will be provided for postnatal women as is currently recommended by the MOHP. In accordance with international recommendation women in the postnatal period will also be offered iron supplementation.

Women will be recruited at antenatal clinics in the Chiradzulu district. Clinics, in which we currently work or have worked, include the Namitambo Health Centre, Chiradzulu Hospital Nguludi Hospital and Mikolongwe clinic. Each clinic books between 50-100 new antenatal clinic attendees per month. We are aware from previous work that there is widespread acceptance within this area of recruitment into research studies both by patients and by staff working in these clinics. From previous experience we would anticipate recruitment rates of at least 150 women per month.

All women are eligible to enter the trial if they so wish if they are less than 24 weeks pregnant by ultrasound scan measurement.

As part of this trial all women who book for antenatal care at the site will be offered a haemoglobin test, malaria test and screening for syphilis (VDRL) at booking. This will also include women who decide not to enter the trial. Azithromycin is not currently recommended for the treatment of syphilis. Women who test positive for VDRL will be offered benzyl penicillin i.m. according to current Malawi Ministry of Health recommendation. We will endeavour to provide testing on site so that women can be offered treatment the same day. Partners of women who test positive for syphilis will be encouraged to come to the health facility for treatment. A second (venous) blood sample will be taken at 30-32 weeks and tests for malaria, haemoglobin and a VDRL will be repeated.

At other follow-up visits screening for anaemia and malaria will be offered. This will involve a finger prick sample of blood being taken only. In the postnatal period (week 1 postnatal or if not attending week 6) women will again be offered screening.

An Ultrasound Scan to estimate gestational age will be offered at booking and repeated at 30-32 weeks. Ultrasonography will also be available for other obstetric indications e.g. failure to feel movement, suspected intrauterine growth retardation, suspected placenta praevia etc. this will be available for all women attending the clinics i.e. not exclusively those who decide to enter the trial. Midwives attending patients will receive extra training so that they are competent to perform these scans.

Women will be encouraged to undergo screening for HIV, with appropriate pre- and post-test counselling, and **nevirapine** will be made available for patients who are HIV positive and who wish to receive nevirapine to reduce mother to child transmission. MSF are currently in process of setting this up in both Nguludi and Chiradzulu Hospitals and we will work together with them. HIV testing will however not be a pre-requisite for recruitment into this trial.

For the study of women and men’s opinion on premature delivery and pregnancy loss, focus group discussions will be organised. We hope to solicit the help of social scientists from Malawi and the Liverpool School of Tropical Medicine for this aspect of the work.

The study period is anticipated to be 3 to 4 years.

### Sample size

With an estimated incidence of 20% of premature labour, in order to detect a reduction from 20% to 15% with 90% power and a 1 tailed test of significance at the 5% level, 987 women are needed per arm. With a 15% dropout rate this would mean a total of 2 270 women recruited into this trial. If the incidence of premature labour should prove to be 15% this sample size will detect a reduction of 4.6% from 15% to 10.4% (with 90% power).

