### Data management and analysis

An independent data safety and monitoring committee (DSMC) will be established to monitor this trial if the trial is approved. Data will be double-entered and verified in Microsoft Access. An interim analysis is planned for which the statistician on the DSMC will be provided with the database. Primary outcome measure is incidence of premature labour (using gestational age as determined by Ultrasound scan at booking and date of delivery). Analysis of the primary outcome will be using a two by two table and Pearson X2 statistic. Secondary outcomes include mean gestational age, perinatal mortality and birthweight. Association with anaemia status, iron status and malaria parisitaemia will be examined using logistic regression.

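### The sample size assumes a one-tailed 5% test, but the named primary test is a Pearson chi-squared; at its usual two-sided 5% level, power is about 83%, not 90%

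*Protocol*

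**What the plan says.** The Sample size section of the protocol gives the basis of the calculation for a fall from 20% to 15%: "with 90% power and a 1 tailed test of significance at the 5% level, 987 women are needed per arm". It continues: "With a 15% dropout rate this would mean a total of 2 270 women recruited into this trial". It adds a fallback: if the incidence turns out to be 15%, the same size is said to have 90% power for a fall to 10.4%.

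The Data management and analysis section fixes the primary test: "Analysis of the primary outcome will be using a two by two table and Pearson X2 statistic". It gives no significance level, critical value or sidedness, and does not say that the p-value would be halved. Neither section gives a reason for one-tailed testing.

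**The concern.** On a two-by-two table the Pearson statistic is the square of the usual z statistic for two proportions, so a rise and a fall of equal size give the same value. Its standard 5% critical value, 3.84, is 1.96 squared, which is a two-sided 5% test with 2.5% in each direction. The one-tailed 5% test in the sample size section uses z = 1.645, or 2.71 on the chi-squared scale, and counts only reductions. As ordinarily applied, these are two different tests.

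Two things are at stake. First, the stated 90% power may not belong to the test that will be run. Second, the rule for declaring the primary result is open. With 987 per arm and an average rate of 17.5%, the standard error under no difference is √(2 × 0.175 × 0.825 / 987) = 0.0171. An observed reduction is then significant from 1.645 × 0.0171 = 2.8 points under the sizing rule, but only from 1.960 × 0.0171 = 3.4 points under the conventional chi-squared rule. A result between the two would be positive or negative according to which section is followed, and that choice could be made after the data are seen.

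**Working it through.** **Inputs, all from the Sample size section:** 20% versus 15%; 90% power (z = 1.2816); one-tailed 5% (z = 1.6449); equal arms; 15% dropout; 2270 recruited; fallback 15% versus 10.4%. One input is an assumption: the two-sided 5% level (z = 1.9600) for the chi-squared test, because the analysis section gives none.

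**Formula** (pooled variance under no difference, no continuity correction), with p̄ the mean of p1 and p2:

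n per arm = [z_α √(2p̄(1−p̄)) + z_β √(p1(1−p1) + p2(1−p2))]² / (p1−p2)²

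**Step 1: reproduce the plan's figure.** For 20% versus 15%, p̄ = 0.175, √(2 × 0.175 × 0.825) = 0.5374 and √(0.16 + 0.1275) = 0.5362.

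- One-sided 5%: (1.6449 × 0.5374 + 1.2816 × 0.5362)² / 0.05² = (0.8839 + 0.6872)² / 0.0025 = 987.2. This is the stated 987.
- Two-sided 5%: (1.0532 + 0.6872)² / 0.0025 = 1211.5, so 1212 per arm.

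Other usual formulas do not blur the distinction: unpooled variance and the arcsine method both give 985 one-sided, and 1209 and 1208 two-sided.

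**Step 2: power of the two-sided 5% chi-squared test.** Power = Φ[(|p1−p2| − z_α·SE0) / SE1], where SE0 and SE1 are the two square-root terms divided by √n.

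- 987 per arm: SE0 = 0.01710, SE1 = 0.01707; (0.05 − 1.9600 × 0.01710) / 0.01707 = 0.965; power 83.3%. One million simulated trials analysed by Pearson chi-squared gave 83.4%. The one-sided value at the same n is 90.0%.
- 2270 × 0.85 / 2 = 965 per arm: SE0 = 0.01730, SE1 = 0.01726; (0.05 − 1.9600 × 0.01730) / 0.01726 = 0.933; power 82.4% (one-sided 89.4%).
- 1135 per arm, nobody lost: 88.0%.

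**Step 3: the fallback, 15% versus 10.4%.**

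- 987 per arm: 86.7% two-sided, 92.3% one-sided.
- 965 per arm: 85.9% two-sided, 91.8% one-sided.
- 1135 per arm, nobody lost: 90.9% two-sided.

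**Step 4: what 987 per arm detects with 90% power, two-sided 5%.** Solving the power formula for the difference from 20% gives 5.5 points (20% to 14.5%), against the 5.0 points stated.

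The planned interim analysis is not reflected in any of these figures.

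**The case against.** The analysis section names a statistic and no level. The only level in the protocol is the one-tailed 5% in the sample size section, and the sizing statement is itself about a reduction. A chi-squared statistic with one degree of freedom can serve a directional test: look at the sign of the difference and reject if the statistic exceeds 2.71. That test has exactly the stated 90% power with 987 per arm, so the two sections could be read together as one coherent one-tailed design. The fallback would then also be sound, at about 92%. Sidedness is, besides, often settled in a statistical analysis plan, and that document is not at hand.

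Much of this stands. The 83% is conditional on the conventional level and must be presented so. What does not follow is that there is nothing to correct. The protocol does not leave the matter open: it fixes a test for sizing and a test for analysis, and in their ordinary meaning the two differ. It nowhere adopts the signed rule needed to reconcile them.

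Two further inferences are tempting and should not be drawn. The objective, "To determine the effects of prophylactic treatment with antibiotic", carries no direction, but it introduces a list of several outcomes and is general wording, not a hypothesis for the primary test; it is weak evidence of two-sided intent. Nor would one-tailed testing leave the trial blind to harm. The primary test could not formally declare an increase in preterm birth, but perinatal mortality is a secondary outcome, an independent monitoring committee and an interim analysis are planned, and women are asked to report side effects.

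**Conclusion.** The point holds as an inconsistency between the sizing and the named primary test. The 987 per arm is a one-sided 5% figure. If the Pearson chi-squared test is read at the conventional two-sided 5% level, power for 20% versus 15% is 83.3% with 987 evaluable per arm and 82.4% with 965, so the chance of missing the target effect is about 17% instead of 10%. For 15% versus 10.4% it is 86.7% and 85.9%.

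A reader might infer that the trial definitely has 83% power, or that it is too small. The protocol supports neither. The level for the final test is not stated, and a declared one-sided rule or a two-sided 10% level would restore 90% with 987 per arm. The figures further assume the protocol's own event rates, equal arms, no continuity correction (with one, two-sided power at 987 is 81.8%) and no adjustment for the interim analysis.

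**What to change.** Make the two sections use the same sidedness and level. The preferred wording:

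- In Data management and analysis, state that the primary Pearson chi-squared test is two-sided at 5%.
- In Sample size, delete the one-tailed wording. State that 987 evaluable women per arm give about 83% power for 20% versus 15% (about 82% with the 965 per arm expected after 15% loss from 2270), or 90% power for a reduction of about 5.5 points from 20%. Restate the fallback as about 86–87% for 15% versus 10.4%.

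This changes wording only; recruitment, data collection and the named test stay as they are. The cost is a less favourable stated power. If the sponsor wants 90% two-sided power for 20% versus 15%, that is a separate decision to enlarge the trial to 1212 evaluable per arm: 2424 / 0.85 = 2852 recruited.

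If the sponsor keeps a one-tailed test, the analysis section must say so, justify it and write down the signed rule. It should also acknowledge that benefit would be claimed at a two-sided p of up to 0.10, and that the primary test could not formally declare an increase in preterm birth.

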**Possible constraints**

Problems with recruitment:

This is a large trial and we may have problems recruiting sufficient numbers of women into the trial. We will establish two teams of midwives who will work at up to four selected sites together with existing staff. As a result of previous work in the district we have established good links both with the communities and staff of the health facilities in this area. Should recruitment be insufficient from the sites chosen we will expand to recruit in two further sites such as Bangwe Health Centre and/or PIM clinic.

Loss to follow up:

We are aware from previous work that it may not be possible to follow up all patients throughout their pregnancies and into the postnatal period. This may be because people decide to discontinue with the trial e.g. because they are not happy to provide a (further) blood sample, because they move or because they lose the index pregnancy e.g. a late miscarriage. All efforts will be made to visit women who are no longer attending clinic at home. Women who wish to discontinue with the trial will continue to receive antenatal and postnatal care provided by the team. From previous experience we estimate a dropout rate of 15% and have adjusted the sample size accordingly.

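### The 15% dropout allowance multiplies by 1.15 instead of dividing by 0.85, so 2,270 women leave about 965 per arm rather than 987 (a minor shortfall)

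*Protocol*

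**What the plan says.** The Sample size section of the Protocol takes 20% as the incidence of premature labour and 15% as the rate to be detected, "with 90% power and a 1 tailed test of significance at the 5% level", and concludes that "987 women are needed per arm". It then allows for loss: "With a 15% dropout rate this would mean a total of 2 270 women recruited into this trial". For a lower incidence of 15% it adds that "this sample size will detect a reduction of 4.6% from 15% to 10.4% (with 90% power". That last sentence does not say whether it means the evaluable or the recruited number, and it does not repeat the sidedness of the test.

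The Possible constraints section, under loss to follow up, describes losses among women already in the trial (stopping participation, moving away, losing the pregnancy) and says: "From previous experience we estimate a dropout rate of 15% and have adjusted the sample size accordingly".

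**The concern.** A dropout rate among enrolled women is a fraction of those recruited. To have a given number left, that number must be divided by the fraction retained. Adding 15% of the evaluable number gives too small a total. The Protocol says the size was adjusted for 15% dropout, but the total given would not leave the 987 per arm that the same paragraph requires. The 987 has no spare margin, so any shortfall takes power below the stated 90%.

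The fallback sentence needs the same check, because it follows directly on these figures and does not say which number or which test it uses.

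**Working it through.** **Inputs.** From Sample size: 20% versus 15%, one-tailed 5%, 90% power, 987 per arm, 2,270 in total (1,135 per arm), fallback 15% to 10.4%. From Possible constraints: 15% dropout. From Methods: recruitment of at least 150 women per month.

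**1. The plan's own 987.** Normal approximation for two proportions, pooled variance under the null, no continuity correction:

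n = [z₁₋α √(2p̄(1−p̄)) + z₁₋β √(p₁(1−p₁) + p₂(1−p₂))]² / (p₁−p₂)²

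With p̄ = 0.175, z₁₋α = 1.645 and z₁₋β = 1.282:
- √(2 × 0.175 × 0.825) = 0.5374
- √(0.16 + 0.1275) = 0.5362
- n = (1.645 × 0.5374 + 1.282 × 0.5362)² / 0.05² ≈ 987.2

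This is 987, or 988 rounded up. The stated figure reproduces.

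**2. The dropout step.**
- 2 × 987 = 1,974
- 1,974 × 1.15 = 2,270.1, which is the stated total
- 1,974 / 0.85 = 2,322.4, so 2,323 are needed (987/0.85 gives 1,162 per arm, 2,324 with equal arms)
- Shortfall: 2,323 − 2,270 = 53 women, or 2.3% of 2,270
- Loss that 2,270 can absorb: 1 − 1,974/2,270 = 13.0%
- Left after 15% loss: 2,270 × 0.85 = 1,929.5, or 964.75 per arm (about 965)

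**3. Power for 20% versus 15%, one-tailed 5%.** Power = Φ{[√n × 0.05 − 1.645 × 0.5374] / 0.5362}
- n = 987: Φ(1.281) = 90.0%
- n = 965: Φ(1.248) = 89.4%

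**4. The fallback, by the same method as step 1.** The rate detectable from 15% with 90% power, one-tailed and uncorrected, is:

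| Per arm | Detectable rate | Reduction | Power for 15% vs 10.4% |
|---|---|---|---|
| 965 | 10.6% | 4.4 points | 91.8% |
| 987 | 10.6% | 4.4 points | 92.3% |
| 1,135 | 10.9% | 4.1 points | 95.0% |

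None of the three gives 10.4%, but in each the power for 15% versus 10.4% exceeds the stated 90%.

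**5. What does give 10.4%.** One- and two-sided tests, with and without continuity correction, were tried at these three sizes. Only one combination matches to the decimal given: two-sided, continuity-corrected, with all 1,135 recruited per arm. There the detectable rate is 10.39%, a reduction of 4.61 points. As a cross-check, 15% versus 10.4% two-sided needs 1,099 per arm uncorrected. The corrected number is 1,099/4 × [1 + √(1 + 4/(1,099 × 0.046))]² ≈ 1,142, or 1,143 rounded up, close to 1,135.

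**The case against.** The best defence is that the slip changes nothing of substance. The 15% is a round estimate from earlier work, and the difference between covering 13.0% and 15% loss lies within its uncertainty. A fall in power from 90.0% to 89.4% would alter no decision, analysis or conclusion. This stands as a statement of size. It does not make the total right: 2,270 comes from the wrong formula, and the text says that the 15% has been allowed for.

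The defence of the fallback is stronger. A reader might infer that the 10.4% is simply wrong, or that 90% power fits no reading of it. The Protocol does not support that. The sentence fixes neither the number nor the sidedness. On the one-tailed reading at 965 or 987 per arm it promises less than the design delivers. On another reading, two-sided with continuity correction at 1,135, it reproduces. That match is an inference; the Protocol does not say the figure was obtained that way. What remains is that the figure is not the 90%-power limit under the method that yields 987. The reading it matches would change the sidedness, add a correction and ignore the dropout just allowed for.

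A reader might also quote the lower power of a two-sided test to make the shortfall look larger. That gap comes from the choice of sidedness, not from the dropout arithmetic. The plan states "a 1 tailed test of significance at the 5% level", and whether that choice is suitable is a separate question.

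**Conclusion.** The dropout allowance is wrong as written. At the stated 15% loss, 2,270 recruited gives about 965 evaluable women per arm instead of 987, and one-tailed power of 89.4% instead of 90%. This assumes equal arms, equal loss in both arms, and 15% meaning a share of those recruited, which is how the Possible constraints section describes it. The effect is minor: 53 women and 0.6 points of power. It does not support a claim that the trial is materially underpowered.

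The fallback is a secondary point of consistency. On the main calculation's basis the limit is about 10.6%. The stated 10.4% errs on the cautious side at 965 or 987 per arm, so it should not be counted as a second arithmetic error.

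**What to change.** Preferably keep 2,270 and state that, after 15% dropout, it gives about 965 evaluable women per arm with 89.4% power for 20% versus 15% on the plan's one-tailed basis. This costs only a change of wording.

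Alternatively, correct the total to 2,323 (1,162 per arm, 2,324 with equal arms). That means 53 or 54 more women. At 150 per month, 53/150 = 0.35 months, or about 11 days of recruitment.

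In either case, put the fallback sentence on the same number and sidedness as the main calculation and state both: 15% to about 10.6%, one-tailed, 90% power. The rounded figure is the same at 965 and 987 per arm, so it suits both options. If 10.4% is to be kept, give the number per arm, the sidedness and any correction on which it rests. This too costs nothing.
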